### Sample

Assuming effective 1:5 average weighting, this gives 19 million patient-months for analysis. Power analysis by simulation (Arnold et al., 2011), accounting for data and model structure indicates that this would be sufficient to estimate a medium effect size (Relative Risk = 0.85)—i.e., 15% relative reduction in the primary outcome attributable to the intervention, with 80% power across these subgroups.

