### Methods

Our primary outcome will be unplanned emergency hospital admissions (outcome 1), secondary outcomes will include: Accident & Emergency (A&E) attendances (outcome 2), 30-day readmission rates (outcome 3), admission to nursing/residential care home (outcome 4), and mortality (outcome 5). The study will analyse the seasonal impacts on hospital admissions during winter.

The study will use quasi-experimental methods and apply two complementary causal approaches: (i) inverse probability of treatment weighted difference-in-differences (IPTW-DiD) (Bettega et al., 2024; Chesnaye et al., 2022; Wei et al., 2023), this is our primary approach to robustly estimate causal effects of telehealth interventions using routinely collected data de-identified by Mersey Care between 2018 and 2024; (ii) To strengthen causal identification, we will also implement regression discontinuity (RD) designs (Thistlethwaite and Campbell, 1960), which are widely adopted in health research (Calonico et al., 2024; Thapa et al., 2025), based on eligibility thresholds derived from the Johns Hopkins ACG risk score (NHS England, 2025d), this is our secondary confirmatory approach. This aspect of the analysis is subject to the availability of Johns Hopkins data. MCTS is commissioned to provide daily care to up to 2,000 patients in Liverpool, 50 patients in Sefton, 100 patients in St Helens, 100 patients in Wirral, and 100 patients in Chesire, respectively. Since the service has not been available over the period to all groups in all parts of Cheshire and Merseyside to construct an appropriate comparator group who did not receive the telehealth service but had similar characteristics (confounders and pre-intervention outcomes) to the patients that did receive it (Barr et al., 2022).

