### Data

The study will use a cohort of monthly data from the Cheshire and Merseyside Secure Data Environment (CM-SDE), the NHS secure data environment that includes linked data across health and care services for all patients registered with a GP in Cheshire and Merseyside. We will use CM-SDE covering a period, 2018–2024 including linked data from the following datasets:

NHS

Primary care dataPrimary care prescribing dataTelehealth services data from the MC telehealth case management system.Secondary care data—Admitted Patient Care (SUS-APC)Community Services Data Set (CSDS)Mental Health Services Data Set (MHSDS)Emergency Care Data Set (ECDS)

Local Authority Adult Social Care

Adult Social Care Dataset (ASCD)

Open data—linked to Lower layer super output areas (LSOAs)

Indices of deprivation

All these datasets are available and can be linked within the CM-SDE. Patient characteristics will reflect individuals at the time of receiving telehealth service and so will correspond to the latest measurement taken during the study period 2018–2024. Table 2 summarises the details of outcome and exposure variables, definition criteria, and datasets from which the variable is derived that would be used in WP1 of the study.

**Table 2 TB2:** Exposure, covariates, and outcome variables for WP1.

Variable category	Variable	Definition/criteria	Data source
Primary exposure	MCTS enrolment	Active enrolment onto the Mersey Care Telehealth Service (Yes/No)	MCTS service dataset
Demographic and baseline characteristics	Age	Age at index date (≥18 years)	SUS-APC
	Sex	Male, Female, Other	SUS-APC
	Ethnicity	White British, Other White, Black, Indian, Pakistani, Bangladeshi, Chinese, Other Asian, Other ethnic group	SUS-APC
	Living alone	Yes/No	Primary Care
	Living with under-18s	Yes/No	Primary Care
	Household size	Number of people in household	Primary Care
	Geography	LSOA 2011	SUS-APC
	Deprivation	IMD 2019	SUS-APC
	Frailty	Fit, mild, moderate, severe frailty	Primary Care
Clinical characteristics	Long-term conditions	Hypertension, cancer, diabetes, CVD, heart failure, CKD, asthma, COPD, depression, schizophrenia, bipolar disorder	Primary Care
Baseline healthcare utilisation	Emergency admissions (previous 12 months)	Count of emergency admissions before index date	SUS-APC
Outcomes	Unplanned emergency hospital admissions	Count of admissions during follow-up	SUS-APC
	A&E attendances	Count of attendances during follow-up	SUS-ECDS

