### Analysis

The study uses two quasi-experimental methods: IPTW-DiD and RD designs. These methods help to reduce the risk of selection bias due to systematic differences between those receiving and not receiving the intervention, in two ways.

The primary approach of the analysis is IPTW-DiD, which is specifically designed to adjust observed differences by reweighting individuals according to their probability of receiving treatment, thereby approximating a pseudo-population in which treatment is independent of observed confounders. The treated cohort will comprise patients who received telehealth, with treatment timing defined by the first quarter in which telehealth was received; patient-quarter observations from this quarter onwards will be considered post-intervention. For untreated patients, comparable index quarters will be assigned to define the pre- and post-intervention periods.

The initial analytic cohort will be restricted to patients aged 50 years or above with at least one relevant long-term condition linked to the telehealth packages: COPD, diabetes, or HF. These eligibility criteria will be applied to both treated and untreated patients to ensure that the control group comprises individuals with a realistic probability of receiving the intervention. To avoid interpreting unobserved quarters as zero healthcare utilisation, the initial analysis will use a balanced panel of patients observed in all 24 quarters across the 6-year study period. The potential selection introduced by excluding patients who die, move away, or register with a GP partway through the study period will be explored in sensitivity analyses.

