Furthermore, the subgroup analyses will be carried out to investigate heterogeneity in the impact of the telehealth intervention across socio-demographic groups. Depending on the size of the subgroup and the availability of data, these analyses will be conducted within the main IPTW-DiD framework using either stratified models or interaction terms. Age, sex, ethnicity, chronic health conditions, frailty score, IMD quintiles, and geographical locations are among the suggested subgroups. For each subgroup, propensity score models and weighting diagnostics will be re-evaluated to ensure appropriate balance. The RD subgroup analyses will be conducted only where there is sufficient sample size close to the eligibility threshold (NHS England, 2025d).

**Work package 2:**  *To determine whether patients using Mersey Care Telehealth Service report improvements in quality of health, mental health, satisfaction, and wellbeing, and whether this varies by sociodemographic group or service delivery type*

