### Methods

Using a prospective study of 2,000 patients accessing MCTS and a comparison group of 2,000 who declined the service. We will gather survey data from telehealth patients on various health metrics, at 1-and 12-weeks post-enrolment, and we will contact patients, monthly, who have recently declined to use the service and collect baseline data and 12-week follow-up data for comparison.

The survey will include measures of health-related quality of life (EQ-5D-3L); Patient Health Questionnaire-9 (PHQ-9); Generalised Anxiety Disorder Questionnaire (GAD-7); Digital Health Literacy Scale (Nelson et al., 2022), and using MCTS standard survey questions, collect information on telehealth care support, patient satisfaction and evaluations on care quality and communication with healthcare professionals. Demographic information for MC telehealth patients is routinely collected. Thus, the survey for the comparator group will gather the following demographic information: health conditions (COPD, HF, and diabetes), age, sex, ethnicity, postcode, English language fluency, number of people living in the household, and reasons for declining the telehealth service for the comparison group to analyse deprivation indices. Our survey questions were based on those used by the Office for National Statistics (Office for National Statistics, 2023).

Our intervention group survey sample size is based on the size of the population of interest (people using the telehealth service), the level of confidence, and the degree of margin of (random) error. Our population is the approximately 22,000 patients who have used the MCTS. With a confidence level of 95%, a sample of 2,000 telehealth patients would provide a margin of error between 2% and 3% in how the responses would represent those of the total population. We feel that this is an acceptable margin of error. For a margin of error of 3% we would require 1,018 responses and so this allows for sufficient loss to follow-up from the target 2,000 participants. As such we require a similar size in the comparator group.

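### The 19 million patient-months behind the WP1 power statement are 1.7 to 2.0 times what the article's own figures allow at 1:5, so the 80% subgroup power claim is unsupported.

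*Protocol article*

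**What the plan says.** All places are in the Protocol article.

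- **WP1, Sample.** "Assuming effective 1:5 average weighting, this gives 19 million patient-months for analysis". A simulation is said to show that this is enough to detect a relative risk of 0.85 "with 80% power across these subgroups". No treated count is printed there.
- **WP2, Methods.** The only total of service users in the article: "Our population is the approximately 22,000 patients who have used the MCTS".
- **WP1, Data.** "We will use CM-SDE covering a period, 2018–2024".
- **WP1, Analysis.** "the initial analysis will use a balanced panel of patients observed in all 24 quarters across the 6-year study period". The cohort is also limited to people aged 50 or over with COPD, diabetes or heart failure.
- **WP1, Analysis (subgroups).** "Age, sex, ethnicity, chronic health conditions, frailty score, IMD quintiles, and geographical locations are among the suggested subgroups".

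**The concern.** The patient-month total should follow from three quantities: treated patients, people per treated patient, and months per person. The article gives a value for each, in different sections, and their product falls well short of 19 million.

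This is the only power statement for the primary outcome, and it extends explicitly to subgroups. The study puts weight on differences by deprivation, ethnicity and place. A reader who accepts 80% power in each subgroup would take a null subgroup result as evidence against an effect. If the data are about half of what was assumed, that reading is not justified.

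**Working it through.** **Inputs**

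| Input | Value | Source |
|---|---|---|
| Stated size | 19,000,000 patient-months | WP1, Sample |
| Ratio | 1:5, so 6 people per treated patient | WP1, Sample |
| Users | about 22,000 ever-users | WP2, Methods |
| Months, primary panel | 24 quarters × 3 = 72 | WP1, Analysis |
| Months, longest window | 7 years × 12 = 84, if both end years are complete | WP1, Data |

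**Step 1: try to reproduce 19 million.** Patient-months = treated × 6 × months.

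- 72 months: 22,000 × 6 × 72 = 9,504,000, which is 50% of 19 million.
- 84 months: 22,000 × 6 × 84 = 11,088,000, which is 58%.
- Counting 5 people instead of 6 per treated patient gives 7,920,000 and 9,240,000, which is further away.

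The ratio of stated to reachable is 19 / 9.504 = 2.0 and 19 / 11.088 = 1.7.

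**Step 2: what 19 million would require.**

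- Treated patients at 1:5: 19,000,000 / (6 × 72) = 43,981, or 19,000,000 / (6 × 84) = 37,698.
- Comparators per treated patient with 22,000 users: 19,000,000 / (22,000 × 72) − 1 = 11.0, or 19,000,000 / (22,000 × 84) − 1 = 9.3.
- Months per person with 132,000 people: 19,000,000 / 132,000 = 143.9, about 12 years.

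None of these matches what the article states.

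**Step 3: direction of the remaining errors.** The 22,000 are all who have ever used a service set up in 2011, so some may fall outside 2018–2024. WP1 then removes people under 50 and anyone not observed in all 24 quarters. Each step can only lower the totals in Step 1.

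**Step 4: effect on the power statement.** The simulated power cannot be recomputed, because the article gives no event rate, alpha, correlation or subgroup sizes. It can only be rescaled. Assume two-sided alpha 0.05 and information proportional to patient-months, and take a subgroup with exactly 80% power at 19 million. Its power at N patient-months is Φ((1.960 + 0.842) × √(N / 19,000,000) − 1.960).

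- N = 11,088,000: Φ(2.802 × 0.764 − 1.960) = Φ(0.18) = 57%.
- N = 9,504,000: Φ(2.802 × 0.707 − 1.960) = Φ(0.02) = 51%.

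**Step 5: is the overall comparison at risk?** This is an illustration on assumed values: 0.01 to 0.03 admissions per patient-month, overdispersion φ of 2 to 5, and half of person-time after the index date. The variance of the log rate ratio in a four-cell difference-in-differences is φ × Σ(1 / events).

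The least favourable case is rate 0.01, φ = 5 and 9,504,000 patient-months. Expected events are 7,920 and 6,732 (treated, before and after) and 39,600 in each comparator period. The standard error is √(5 × 0.000325) = 0.040. Power is Φ(0.1625 / 0.0403 − 1.960) = 98%.

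Under the same assumptions, the smallest share of the cohort that reaches 80% power rises from about 3–24% at 19 million to about 6–48% at 9.5 million.

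**The case against.** **The 22,000 belongs to WP2.** The Sample section prints no treated count, and its wording points back to text that is not there, so material was probably lost in condensing the protocol. This stands as a limit: the simulation itself is not shown to have used a wrong number. It does not remove the conflict, because an ever-user total is already generous for WP1. Commissioned capacity does not reach the required count either. If all places were full from each documented start to December 2024, with 5-month turnover and no re-enrolment, the count would be 33,600 (Liverpool) + 800 (St Helens) + 300 (Sefton) + 400 (Wirral) + 220 (Cheshire West) = 35,320, still below 37,698. That is only an illustration: five months is not a fixed duration, shorter stays would raise the count, and Table 1 warns that its dates may differ from true enrolment.

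**Weighting can use a larger untreated pool than five per treated patient.** True, and 5:1 matching is only a fallback. But the Sample section derives its figure from an effective 1:5 ratio, so a larger raw pool does not repair that sentence.

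**Subgroup analyses depend on size.** The subgroups are suggestions, the choice of model depends on subgroup size, and the Discussion says subgroups will be formed so that numbers suffice. This reduces the risk of misreading. It also sits awkwardly with 80% power already claimed for them.

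**Stronger readings that a reader might infer, and that the article does not support:**

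- *Small localities have a calculable low power.* Sefton has 50 places and Cheshire West 100, but a power figure needs an assumed turnover and an assumed admission rate. The 37% risk is a case-finding threshold, not a mean. Sefton's result changes sides of 80% under modest changes to the rate.
- *Cheshire West drops out of the panel entirely.* That requires a panel starting in Q1 2018, and no start quarter is given.
- *Analysing patient-quarters loses further information.* Monthly data grouped into quarters is a change of unit.
- *The factor of two reveals double counting.* 22,000 × 12 × 72 and 22,000 × 6 × 144 both give 19,008,000, so the match does not identify a cause.

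**Conclusion.** The concern holds as a conflict among stated figures. At 1:5, the article's own inputs allow at most 9.5 million (72 months) to 11.1 million (84 months) patient-months, against 19 million stated. The overstatement is 1.7 to 2.0 times before any exclusion. It rests on 22,000 being a fair ceiling for the treated count, since it is the only user total given.

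The 80% power claimed for subgroups is therefore unsupported. On the scaling assumptions of Step 4, a subgroup just meeting 80% at 19 million would have about 51% to 57%. This is not a demonstration that any named subgroup falls below 80%; the article lacks the event rate, correlation and subgroup sizes needed.

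Nor should a reader infer that the primary comparison is underpowered. Under the illustrative rates it keeps at least 98% power at 9.5 million patient-months, before the exclusions. The consequence falls on the subgroup statement.

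**What to change.** In WP1, Sample:

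1. State the treated count, the months per patient and the ratio that produce the patient-month total.
2. Correct 19 million, or whichever input conflicts with it, so that it matches the cohort in WP1, Analysis: aged 50 or over, with a relevant condition, and observed in all 24 quarters.
3. Re-run the existing simulation on that cohort.
4. Restate power, or the detectable relative risk, overall and for each named subgroup.
5. Remove "with 80% power across these subgroups" wherever 80% is not met, and label those analyses as estimation only.

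The cost is one re-run of a simulation that already exists and a less favourable published figure. The data are retrospective, so no extra patients are needed and the primary analysis does not change.

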### Analysis

The study uses two quasi-experimental methods: IPTW-DiD and RD designs. These methods help to reduce the risk of selection bias due to systematic differences between those receiving and not receiving the intervention, in two ways.

The primary approach of the analysis is IPTW-DiD, which is specifically designed to adjust observed differences by reweighting individuals according to their probability of receiving treatment, thereby approximating a pseudo-population in which treatment is independent of observed confounders. The treated cohort will comprise patients who received telehealth, with treatment timing defined by the first quarter in which telehealth was received; patient-quarter observations from this quarter onwards will be considered post-intervention. For untreated patients, comparable index quarters will be assigned to define the pre- and post-intervention periods.

The initial analytic cohort will be restricted to patients aged 50 years or above with at least one relevant long-term condition linked to the telehealth packages: COPD, diabetes, or HF. These eligibility criteria will be applied to both treated and untreated patients to ensure that the control group comprises individuals with a realistic probability of receiving the intervention. To avoid interpreting unobserved quarters as zero healthcare utilisation, the initial analysis will use a balanced panel of patients observed in all 24 quarters across the 6-year study period. The potential selection introduced by excluding patients who die, move away, or register with a GP partway through the study period will be explored in sensitivity analyses.

A treatment model will calculate the likelihood of each patient receiving the intervention using baseline socio-demographic variables, comorbidity measures, and 12-month cumulative pre-intervention healthcare utilisation, such as unplanned emergency admissions. For variables that may change over time, baseline or pre-intervention values will be used. Stabilised IPTW weights (Austin and Stuart, 2015) will be used in the DiD model to balance measured baseline covariates and reduce the influence of extreme weights. Covariate balance, weight stability, overlap/common support, effective sample size, and the plausibility of the conditional parallel-trends assumption will be assessed using weighting diagnostics and pre-intervention outcome trends. Comprehensive sensitivity analyses will be performed to evaluate the robustness of all estimates.

To manage the potentially large untreated population, the above eligibility restrictions will be applied before weighting. If the remaining comparison cohort is still too large for the available computing environment, a 5:1 propensity-score matched comparison cohort based on baseline characteristics may be constructed before applying the weighting approach; this will be reported as a computational sensitivity analysis.

Additionally, the RD design (Thistlethwaite and Campbell, 1960) will serve as a secondary complementary analysis, subject to the availability of a documented Johns Hopkins ACG risk score eligibility threshold (NHS England, 2025d) and sufficient observations close to that threshold. Threshold values, temporal changes, and geographical variations will be documented. As RD estimates a local effect among patients close to the eligibility threshold, its findings will be interpreted alongside, rather than as direct confirmation of, the IPTW-DiD estimates.

Furthermore, the subgroup analyses will be carried out to investigate heterogeneity in the impact of the telehealth intervention across socio-demographic groups. Depending on the size of the subgroup and the availability of data, these analyses will be conducted within the main IPTW-DiD framework using either stratified models or interaction terms. Age, sex, ethnicity, chronic health conditions, frailty score, IMD quintiles, and geographical locations are among the suggested subgroups. For each subgroup, propensity score models and weighting diagnostics will be re-evaluated to ensure appropriate balance. The RD subgroup analyses will be conducted only where there is sufficient sample size close to the eligibility threshold (NHS England, 2025d).

**Work package 2:**  *To determine whether patients using Mersey Care Telehealth Service report improvements in quality of health, mental health, satisfaction, and wellbeing, and whether this varies by sociodemographic group or service delivery type*

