Using the Combined Intelligence for Population Health Action (CIPHA) dataset, a regional population health data platform that links routinely collected health and care records (including primary care, hospital, and community data) to support population risk stratification and service planning, patients eligible for the service are identified through established case-finding processes. Patients must be aged 18 years or older, have a confirmed diagnosis, and reside within a commissioned area. Eligibility and case-finding evolved during the study period. Prior to January 2024, identification of potentially eligible patients relied on the Welsh Predictive Model alongside existing clinical caseloads, referral pathways, and clinical judgement. From January 2024, the CIPHA Enhanced Case Finding Tool incorporating the Johns Hopkins Adjusted Clinical Groups (ACG) risk stratification system was introduced. Patients with an estimated six-month risk of emergency hospital admission of 37% or greater may be identified as suitable for telehealth review, subject to clinical assessment and pathway-specific eligibility criteria. As eligibility criteria and case-finding approaches changed over time, the clinical risk profile of patients enrolled in the service may have varied across the study period.

Although the Johns Hopkins ACG risk score (Johns Hopkins University, 2014) is used operationally to support case finding, it is not available for the wider eligible population included in the evaluation dataset and, therefore, cannot be used directly for comparator selection or matching. Consequently, analyses will adjust for available demographic, clinical, socioeconomic, locality, and prior healthcare utilisation characteristics as proxies for baseline risk.

Patients enrolled in MCTS receive a home remote-monitoring package (Doc@Home, Graphnet Ltd), with setup support provided in person, by telephone, or through written guidance. Patients submit daily symptom and physiological readings (e.g., oxygen saturation for COPD and weight and blood pressure for HF) via a mobile app or an NHS-provided device. Monitoring usually happens Monday through Friday for up to 5-months which represents the standard initial monitoring and review period within the telehealth pathway rather than a fixed maximum duration for all patients. Patients may be discharged, extended, stepped down, or re-enrolled according to clinical need and pathway-specific criteria.

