The primary exposure is active enrolment onto the MCTS. Referral alone will not constitute exposure, as not all referred patients commence telehealth monitoring. For enrolled patients, the index date will be defined as the date on which active telehealth monitoring begins. To account for temporal variation in healthcare utilisation and service delivery, telehealth enrolment dates will be grouped into calendar quarters (Q1: January–March; Q2: April–June; Q3: July–September; Q4: October–December). Comparator patients will be selected from quarterly eligibility snapshots comprising individuals who were eligible for MCTS, alive, and registered during the same quarter but who did not enrol onto the service. Calendar quarter will be used as an exact matching variable within the propensity score matching process, ensuring that telehealth participants are compared only with eligible non-enrolled patients observed during the same time period. Additional demographic, clinical, risk, and baseline healthcare utilisation variables will be incorporated into the matching procedure. This approach aims to minimise temporal bias arising from changes in healthcare utilisation, seasonal pressures, COVID-19 recovery effects, admission practices, and service delivery over the study period. The primary analysis will therefore estimate the effect of active enrolment onto MCTS compared with eligible non-enrolment during the same calendar quarter. Findings should be interpreted as representing the effect of the telehealth service model as delivered in routine practice rather than the effect of referral alone or any individual intervention component.

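### WP1 defines its comparators in two unreconciled ways, and the Analysis wording, read plainly, selects them on never enrolling later

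*Protocol article*

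**What the plan says.** The comparator is described in two sections of the protocol article.

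- **WP1, Methods.** Comparators come from quarterly snapshots of people "eligible for MCTS, alive, and registered during the same quarter but who did not enrol onto the service". The closing clause has no time limit: it could mean not enrolled in that quarter, or never enrolled. The section then says that the primary analysis will "estimate the effect of active enrolment onto MCTS compared with eligible non-enrolment during the same calendar quarter", which leans towards the same-quarter meaning.
- **WP1, Analysis.** "The treated cohort will comprise patients who received telehealth, with treatment timing defined by the first quarter in which telehealth was received". Quarters from then on count as post-intervention. The text continues: "For untreated patients, comparable index quarters will be assigned to define the pre- and post-intervention periods". No rule lets a person who enrols late serve as a comparator at an earlier quarter, and none says when such a person's comparator time would end.

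Two other parts of the article bear on this. The service description ties enrolment to admission risk: before January 2024 a predictive model was used alongside caseloads, referrals and clinical judgement, and since then "Patients with an estimated six-month risk of emergency hospital admission of 37% or greater may be identified as suitable for telehealth review". WP1 Analysis bases the treatment model on baseline variables and 12-month pre-intervention utilisation, checks pre-intervention outcome trends, and names sensitivity analyses for exclusion through death, moving away and late registration.

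**The concern.** If untreated means never enrolled, comparator status at a given index quarter depends on what happens afterwards. Take two eligible patients with the same history who are both unenrolled in quarter 8. One stays well and never enrols. The other has several admissions, is picked up by case finding and enrols in quarter 12. Both are valid comparators at quarter 8, but only the first is kept. The comparators' post-index admission rate is then lower than that of the population they are meant to represent. Treated patients are not screened on later enrolment in this way.

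The planned safeguards look in the wrong place. Weighting balances what was known before the index quarter, and trend checks examine the period before it, whereas this selection acts after it. Weighting may even sharpen the problem, because untreated patients who most resemble enrollees get the most weight and are also the most likely to enrol later. What is at stake is the primary WP1 estimate, for which the Sample section takes a relative risk (RR) of 0.85 as its target.

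**Working it through.** The article gives no figure on this point to reproduce. It states neither the share of the eligible pool that ever enrols nor how strongly enrolment follows admissions. Both are assumed below, and the RR of 0.85 from the Sample section serves as the yardstick.

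**1. Algebra.** Let f be the share of the weighted comparators, valid at the index quarter, who enrol later. Let m be the post-index admission rate of never-enrollers and k·m that of later enrollees. The full pool has mean (1 − f)m + f·k·m, and the never-enrolled pool has mean m. Dropping later enrollees therefore multiplies the estimated RR by

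1 − f + f·k.

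| f | k | Multiplier | A true 0.85 reads |
|---|---|---|---|
| 1% | 2 | 0.99 + 0.02 = 1.01 | 0.858 |
| 5% | 1.5 | 0.95 + 0.075 = 1.025 | 0.871 |
| 5% | 3 | 0.95 + 0.15 = 1.10 | 0.935 |
| 10% | 1.5 | 0.90 + 0.15 = 1.05 | 0.892 |
| 10% | 2 | 0.90 + 0.20 = 1.10 | 0.935 |
| 10% | 0.8 | 0.90 + 0.08 = 0.98 | 0.833 |

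The bias runs against the service when k is above 1, which is what risk-driven enrolment implies. It reverses if k is below 1.

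**2. Simulation.** All settings are assumptions.

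- 400,000 patients over 24 quarters, with Poisson admissions at a base of 0.06 per quarter.
- Log-normal stable risk (SD 0.6) and a fluctuating component (SD 0.7, quarter-to-quarter correlation 0.8).
- Quarterly enrolment probability p0 × (1 + 3 × min(admissions in the last 4 quarters, 4)), with p0 varied to change the share ever enrolled.
- Treated and comparator patients balanced on the 12-month pre-index count within quarter, and 8 quarters of follow-up.

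With no true effect, repeated runs gave:

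| Share ever enrolled | RR against never-enrolled |
|---|---|
| 2 to 5% | 1.00 to 1.02 |
| 10 to 12% | about 1.04 to 1.06 |
| 18 to 22% | about 1.11 to 1.14 |

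Comparators defined as not yet enrolled at the snapshot gave about 0.98 to 1.01. With a true RR of 0.85, never-enrolled comparators gave about 0.91 at 12% and 0.97 at 22%; not-yet-enrolled comparators gave 0.86 in both. A difference-in-differences ratio (post over pre, treated over comparator) stayed within 0.005 of the simple ratio, so differencing does not remove the bias.

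**3. Isolating the cause.** When enrolment did not depend on admissions, the two comparator definitions agreed. The gap therefore comes from later enrolment following deterioration.

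**4. Sensitivity to the assumptions.** A second model, with enrolment rising exponentially in prior admissions and 4 quarters of follow-up, gave null RRs of 1.015, 1.05 and 1.15 at 3%, 9% and 12% ever enrolled. The enrolment rule matters as much as the enrolment share. In the same model, admitted patients were then allowed to pass into a state that bars enrolment while still counting as untreated. The null RR against never-enrolled comparators fell to 0.99 or 0.95, depending on how often this happened.

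**The case against.** The strongest reply is that the article nowhere says never enrolled. WP1 Methods, which sets out comparator selection, states a same-quarter contrast that would admit later enrollees, and the later-enrollee rule could sit in a fuller document. This stands in part: a reader might infer that the protocol has settled on never-enrolled comparators, and it has not. But the Analysis section does not carry the same-quarter rule through, and its once-per-patient classification points the other way. That conflict is in the stated design, not a detail left out.

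Second, the size is uncertain and may be small. The 1:5 ratio in the Sample section and the optional 5:1 matching suggest that enrollees are at most about 1 in 6 (17%) of the pool, so scenarios above that are probably high. Non-enrolment also has causes unrelated to deterioration: "Since the service has not been available over the period to all groups in all parts of Cheshire and Merseyside". Table 1 shows GP referral and step-down routes as well as risk-based case finding, and the 37% threshold applies only from January 2024, late in the 2018–2024 data. All of this stands, and it is why the size is given as a range.

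Third, a reader might infer that WP1 as a whole is biased against the service. The documents do not support that. Enrolment after a peak in admissions can favour the service through regression to the mean. Case finding in Table 1 requires a negative nursing-home flag that the Analysis cohort restriction does not repeat, so some of the sickest patients may remain untreated. The "balanced panel of patients observed in all 24 quarters across the 6-year study period" also filters both groups on survival, which the simulation does not model.

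The possibility of offsetting biases is not a reason to keep one that can be removed. None of these points gives the pre-index adjustment a way to remove it.

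**Conclusion.** The point holds as an inconsistency with a consequence. Methods and Analysis define the WP1 comparator differently, and the Analysis wording, read plainly, selects comparators on their course after the index quarter. The planned weighting and trend checks neither correct nor detect this, and the named sensitivity analyses do not cover it.

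Taken alone, the component raises the RR, against the service. At the low enrolment shares simulated it is minor. At 10 to 12% ever enrolled, a true 15% reduction would read as roughly 9 to 10% in the main simulation. A claim that the target effect would be hidden or reversed needs enrolment shares, or a dependence of enrolment on admissions, that the article does not document. These sizes rest on assumed enrolment behaviour and on later enrollees having more post-index admissions than never-enrollers. The net direction of bias in WP1 is not established.

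**What to change.** In both WP1 Methods and WP1 Analysis:

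1. Define a comparator as any eligible patient not enrolled up to and including the snapshot quarter, regardless of later enrolment.
2. Let later enrollees enter the treated cohort at their own index quarter, and cluster by patient because one person can contribute to both groups.
3. Fix in advance how a comparator's time after enrolment is handled. Either keep it over a fixed follow-up window, or censor at enrolment with weights for that censoring. Both are defensible; unweighted censoring would bring back selection on deterioration.
4. Report the share of comparators who cross over.
5. Use never-enrolled comparators only as a sensitivity analysis.

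This takes protocol wording and cohort-building code, with no new data, and should be done before any estimate is seen. The cost is some dilution if post-enrolment time is kept, or extra modelling if it is censored. In the simulation, 6 to 20% of comparators enrolled within 8 quarters (at 12 to 38% ever enrolled), yet a true 0.85 still read 0.86 to 0.87. A shorter window reduces the dilution.
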